### Objectives

This paper describes the protocol of a pragmatic randomized controlled trial (RCT), PAC-WOMAN, targeting Portuguese post-menopausal women diagnosed with hormone-receptor-positive breast cancer, currently on Aromatase Inhibitors. This project primary aims are:a) To develop and test the long-term (16-month) effectiveness and cost-effectiveness of two 4-month group-based interventions, compared to a control waiting list, on promoting sustained changes in PA, sedentary behavior, QoL, and healthcare services’ use (primary outcomes)b) To compare the effects of both interventions (i.e., brief PA counseling vs. structured exercise) on long-term changes in our primary outcomes, as well as their cost-effectivenessc) Evaluate pretreatment moderators of 4-month and 16-month changes in PA, sedentary behavior, and QoLd) Identify critical motivational (theoretical) mechanisms of change in PA, sedentary behavior, and QoL, and explore their mediating role.

As secondary aims, we will study the impact of both interventions on AI therapy continuation, adverse events of treatment, disease-free survival, body composition, sleep quality, physical parameters (e.g., muscular strength), and psychosocial factors (e.g., body image). Furthermore, process evaluation will also be conducted seeking to analyze implementation facilitators and barriers.

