#### Study design and setting

PAC-WOMAN is a three-arm, superiority parallel-group, pragmatic randomized controlled trial (RCT), comprising a 4-month intervention period and a 12-month follow-up, that will be conducted to evaluate the effectiveness of two interventions aimed at promoting active lifestyles and improved quality of life in the long-term, albeit with different approaches (brief PA counseling vs. supervised structured exercise), compared to a control group.

Clinical trials can be conceptualized across a continuum from explanatory to pragmatic, with the former assessing if a program could work under ideal circumstances and the latter determining if it could work in real world conditions. Pragmatic trials are necessary for developing and testing interventions using the settings, resources, patients, and approaches to which they will ultimately be implemented [51, 52], thus ensuring that research funds have the greatest potential to impact patient and population health and have therefore been recommended [53].

This project will be conducted under real world circumstances at a main urban center served by several hospitals. Interventions were designed to take place at local gyms, with facilitated accessibility and appropriate equipment and facilities. Recruitment of participants is taking place via dissemination of the trial in main hospitals with oncology centers. A schematic description of the study phases and participant’s timeline, according to SPIRIT, is presented in Table 1. Participants will be enrolled in cohorts or “waves”. Ethics approval was obtained prior to study development/implementation from the faculty responsible for the study (FEFD: M25C21) and all recruitment hospitals (CAML: 285/21; HFF: 10/2022; IPOLFG: UIC/1499; CHLO: 2281). The trial is being conducted in accordance to the declaration of Helsinki for human studies from the World Medical Association [54].

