#### Randomization and blinding

After signing the informed consent and completing the baseline assessments, participants are randomly allocated to one of the three arms. Allocation is being made according to an automated computer-generated randomization scheme performed by a member of the research team not directly involved with participants. Adjustments in the allocation ratios might be made if recruitment takes longer than expected and interventions are required to start for timely reasons. Group assignment is only communicated to participants after all baseline testing is finished.

Participants and research team staff are unaware of group allocation at the time of recruitment and baseline assessments because randomization is only performed after participants have completed baseline assessments. This study will involve behavior change interventions, preventing any concealment of group allocation after randomization from either participants or intervention counsellors. Nonetheless, participants will be blinded to the study rationale. Also, to minimize bias, physical activity and sedentary behavior (primary outcomes) are objectively assessed using accelerometers and psychometric data are collected by self-report and introduced in the Qualtrics platform in its raw state. All outcome data will be kept blinded until the final data entry for the entire study is completed.

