#### Interventions

The brief PA counseling (PAC) program will comprise 8 sessions (120 min each), every fifteen days, addressing the following themes: reasons to change, an introduction to the PAC-WOMAN program and principles, types of physical activity and their benefits, strategies on how to become more active and less sedentary, how to safely practice exercise at home, the importance of social support for doing more physical activity, barriers and facilitators for becoming more active, development of coping plans and strategies to overcome those barriers, establishing SMART goals, self-monitoring, medical aspects related to symptom management in breast cancer survivors, body image and self-acceptance, sharing experiences with role models, and re-evaluating action plans.

To increase the potential for long-term behavior change, it is important to target theoretically proposed mechanisms of change and incorporate evidence-based behavior change strategies. Self-Determination Theory (see Rationale for the PAC-WOMAN trial), and several evidence-based behavior change techniques, will be used throughout the intervention. The goal will be to empower participants to develop self-regulation resources, fueled by autonomous motivation to integrate physical activity into daily lives, even in the face of adversity, and thus sustain changes in physical lifestyle. The basic psychological needs of autonomy, competence, and relatedness [28] will be supported in all sessions and intervention materials. More specific SDT-based behavior change strategies will include the provision of choice, meaningful rationale, connection between participants’ health behavior and deep inner values, goal setting, action planning, self-monitoring, coping planning, weighing pros and cons of change in the context of held values and life priorities. Group-based sessions will allow the exchange of experiences, feelings, difficulties, and effective solutions to overcome them, in a respectful, non-judgmental, and supportive environment. The portfolio of strategies, and intervention motivational climate, is in accordance with systematic reviews in this regard [41]. Exercise professionals, previously trained in brief counseling skills for health behavior change and its implementation, will deliver the sessions.

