A participants’ manual was developed, including a toolbox supporting each session. An activity tracker will be provided to all participants to facilitate self-monitoring. An Exercise Booklet was also created, including different exercises that can be performed at home, accompanied by QR codes with complementary instructive videos. An invested role model (a women previously diagnosed with breast cancer) will illustrate the exercises in the booklet during one of the sessions to show the easiness of their completion. Participants will be prompt to use the booklet as they see fit, during their daily lives, in an integrated fashion (passible to be integrated in the long term) and at a self-selected pace.

The structured exercise program was designed based on the most recent guidelines for exercise prescription and safe practice in cancer populations [12, 19, 59]. A group-based supervised program comprising 32 sessions (over 4 months), lasting 90 min each, and taking place twice a week, was developed. The program combines mobility, aerobic, and strength exercises, respecting a periodization model of four mesocycles of 8 sessions, with progressive intensity and complexity, following the periodization model for each exercise component. Once every 15 days, a thematic group class will be offered to participants, so that they can explore different physical activities and enhance their exercise experience.

Each session will be organized into four components: (i) warm-up—a 10 to 30-min combination of articular mobility exercises and body weight activities; (ii) muscular strength—30 to 45 min, 6–7 large muscle group exercises with an intensity of 60–80% of one maximal repetition (10–15 repetitions, 2–3 sets); (iii) aerobic training—20 to 30 min of a cardiorespiratory workout modality chosen according to participant’s preferences (treadmill, elliptic, bike and row machine) with an intensity of 40–60% of reserve heart rate; (iv) cool-down (5 min). Group sessions will be provided in a person-centered, positive interpersonal environment, by qualified exercise professionals.

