#### Statistical methods

Factorial Anovas with repeated measures, adjusting for potential covariates (e.g., primary treatment, length of AI therapy), will be conducted for primary and secondary outcomes. The analysis will be intent-to-treat to include compliance effects in the overall assessment. Last Observation Carried Forward will be used to impute missing values. A per-protocol analysis will also be conducted without participants who do not attend at least 80% of the sessions. Normality plots and Kolmogorov–Smirnov tests will be used to test normality of outcome variables. If substantial departure from normality is found, square root log transformations will be computed. If normality is still not satisfied, non-parametric tests (e.g., Kruskal–Wallis) will be employed. As the experimental design is factorial, multiple comparison adjustments will not be appropriate.

Mediators of change, i.e., mechanisms by which participants change their lifestyle behaviors and QoL (vs. controls), will be explored using structural equation modeling (AMOS 18.0) and multiple mediation analysis (PROCESS macro v. 3.3 for SPSS). Putative candidates will include motivational (e.g., autonomous motivations) and self‐regulatory (e.g., action planning) variables. Mediation is said to occur when the causal effect of an independent variable (X) on a dependent variable (Y) is partially or fully explained by a mediator (M) [93]. Indirect effects will be tested using Preacher and Hayes’ procedures [94]. Bootstrapping with 5000 samples and 95% CI estimates for indirect effects will be calculated and assumed significant (α = 0.05) if the CI does not encompass zero [95, 96]. The ratio of the indirect effects to the total effects (P_*M*_) will be calculated to express the strength of the mediation effects [95]. Moderators, i.e., baseline characteristics that have an interactive effect with the intervention on the outcome(s), will be assessed to better understand individual differences in intervention effects [97, 98]. Moderation effects on primary outcomes will be conducted at intervention or follow-up’s end.

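### PAC and StEx are delivered in groups, but the planned ANOVA and the sample size treat all women as independent; any within-group correlation makes standard errors too small, most of all for PAC vs StEx

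*Protocol article*

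**What the plan says.** The Objectives describe "two 4-month group-based interventions, compared to a control waiting list", and aim b is a direct contrast of the two active arms: "To compare the effects of both interventions (i.e., brief PA counseling vs. structured exercise) on long-term changes in our primary outcomes".

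The Interventions section confirms group delivery in both arms. For PAC, "Group-based sessions will allow the exchange of experiences, feelings, difficulties, and effective solutions to overcome them". For StEx, "A group-based supervised program comprising 32 sessions (over 4 months), lasting 90 min each, and taking place twice a week, was developed". The waiting-list women carry on with usual care and belong to no delivery group.

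Under Randomization and blinding, "participants are randomly allocated to one of the three arms", so the unit of randomisation is the woman. Enrolment is in waves (Study design and setting), and the Table 1 legend lists three cohorts.

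Under Statistical methods the outcome model is fixed as follows: "Factorial Anovas with repeated measures, adjusting for potential covariates (e.g., primary treatment, length of AI therapy), will be conducted for primary and secondary outcomes". In the Participants section the sample size is based on a repeated-measures ANOVA, reaches 98 including 25% dropout, and is raised to 122 for the mediator and moderator analyses. Neither section, nor the list under Potential covariates, mentions delivery group, facilitator or cohort.

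**The concern.** Women who spend four months in the same group share its dynamics and the way its sessions were run. For PAC, learning from one another is an intended part of the treatment. The protocol also lets session order and spacing change in response to participants' feedback and has facilitators log deviations, so two groups in one arm may not receive quite the same thing. Outcomes can then be more alike within a group than between groups of the same arm, while controls remain independent individuals. This is a partially nested design.

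A repeated-measures ANOVA with patient-level covariates counts each woman as an independent replicate of her arm. Chance differences between a handful of groups can then be read as differences between interventions. PAC vs StEx, a stated primary aim, is the most exposed because both sides are grouped.

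**Working it through.** **The plan's own figure.** No numeric effect size or within-person correlation is given. With assumed values f = 0.15 and correlation 0.5, three arms and four measurements, the G*Power within-between interaction formula (noncentrality f² × N × 4 / (1 − 0.5)) gives N = 78 for 80% power. Then 78 × 1.25 = 97.5, rounded to 98, and 98 × 1.25 = 122.5, stated as 122. Other inputs come close too, so this is one reading. It contains no allowance for clustering.

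**Inputs for the check**
- N = 122, three arms (protocol). Equal allocation is assumed, since no ratio is stated and "Adjustments in the allocation ratios might be made if recruitment takes longer than expected"; this gives 122/3 = 40.7 per arm.
- Groups per active arm: not stated. Scenario A is one group per arm in each of three cohorts, 122/9 = 13.6 women. Scenario B is six groups per arm, 122/18 = 6.8 women.
- ICC after baseline: not stated; range 0.02 to 0.10 assumed, equal in both active arms.

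**Formulas**
- PAC vs StEx: DE = 1 + (g − 1) × ICC.
- Active arm vs control: DE = 1 + (g − 1) × ICC / 2, because only one side is clustered.
- Actual error of the unadjusted two-sided 5% test: 2 × (1 − Φ(1.96/√DE)).

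**Example.** Scenario A, ICC 0.05, PAC vs StEx: DE = 1 + 12.56 × 0.05 = 1.63; √DE = 1.28; 1.96/1.28 = 1.54; error 12.5%.

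| Scenario | ICC | DE, PAC vs StEx | Error, PAC vs StEx | Error, active vs control |
|---|---|---|---|---|
| A: 3 groups of 13.6 | 0.02 | 1.25 | 8.0% | 6.5% |
| A | 0.05 | 1.63 | 12.5% | 8.7% |
| A | 0.10 | 2.26 | 19.2% | 12.5% |
| B: 6 groups of 6.8 | 0.02 | 1.12 | 6.4% | 5.7% |
| B | 0.05 | 1.29 | 8.4% | 6.7% |
| B | 0.10 | 1.58 | 11.9% | 8.4% |

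**Simulation.** An ordinary t-test over 40,000 trials per setting gives 8.0% / 12.9% / 19.7% for PAC vs StEx with 3 groups of 14, and 6.5% / 8.8% / 12.7% with 6 groups of 7. A repeated-measures interaction, closer to the planned test, gives 11.7% with 3 groups of 13 and 8.4% with 6 groups of 7 at ICC 0.05. With ICC 0 all are about 5%.

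**When 10% is reached.** This needs DE = (1.96/1.645)² = 1.42. Solving 1 + (g − 1) × ICC = 1.42 gives an ICC of 0.033 for groups of 13.6 and 0.073 for groups of 6.8. If scenario A groups shrink by 25% to 10.2, it is 0.046.

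**Information.** In scenario A at ICC 0.05, each active arm of 40.7 carries the information of 40.7/1.63 = 25 women for PAC vs StEx. The control arm loses nothing.

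**The case against.** The strongest reply is that every figure rests on inputs the protocol does not give. This stands. The three cohorts come from the legend of a table that is not shown, and nothing says that each cohort had one group per arm. A reader might infer that the PAC vs StEx error does exceed 10%. The documents do not support that: with smaller groups, or an ICC of 0.02 or less, it stays at roughly 6 to 8%.

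A reader might also infer that every comparison is too optimistic. That is too strong. If each wave fills all arms, variation shared across arms cancels in the contrast. With a shared cohort variance of 0.05 and no group effect, simulation gives 4.5%, slightly conservative. Only group-specific variation inflates the error.

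Nor does the protocol say how facilitators, gyms or time slots map to groups. Peer exchange is described as an ingredient of PAC, while StEx has individualised intensity, so equal ICCs are an assumption. The main aim is at 16 months, a year after the groups end, and clustering may have faded. Against that, the process evaluation asks how far participants still interact with their peers after the programme.

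Finally, this is a condensed article, its covariate list is open-ended, and an analysis plan may add a random effect. This lowers certainty but does not remove the point: the article names the model for all primary and secondary outcomes, and that model assumes independence between women.

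**Conclusion.** The point holds in conditional form. As written, the analysis and the sample size ignore correlation among women treated in the same group, and the protocol itself gives reasons to expect some. If there is positive group-specific correlation after baseline, standard errors are too small. For PAC vs StEx, a nominal 5% test has an actual error of about 8% / 13% / 20% at ICC 0.02 / 0.05 / 0.10 with three groups of about 14 per arm, and about 6% / 8% / 12% with six groups of about 7. An active arm against control is less affected: about 6.5 to 9% at ICC 0.02 to 0.05 with the larger groups. ICC, group size, number of groups and equal allocation are all assumptions. The protocol should address clustering, but it does not show that the error is above any particular level.

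**What to change.** 1. Record a delivery-group identifier for every PAC and StEx participant. The facilitators' logbooks already hold session attendance, so membership should be recoverable.
2. Analyse each follow-up adjusted for the baseline value, with a random effect for delivery group in the PAC and StEx arms only and each control as her own singleton. Use Satterthwaite or Kenward-Roger degrees of freedom and report the ICC.
3. If a repeated-measures model over all four time points is kept, use a post-baseline group-by-time random effect. A group intercept that is constant over time cancels out of the arm-by-time contrast and leaves the test uncorrected. In a small check (40 simulated trials, 3 groups of 14, post-baseline ICC 0.10), the mean arm-by-time standard error was 0.2172 with such an intercept and 0.2171 without.
4. If there are too few groups to estimate the ICC stably, report contrasts with standard errors inflated for ICC 0.02 and 0.05 beside the unadjusted ones. In scenario A the factors √DE are 1.12 and 1.28 for PAC vs StEx, and √1.13 = 1.06 and √1.31 = 1.15 for an active arm vs control. Use the actual group sizes.

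This needs analysis work only, with no extra women or visits. Outcome data are to stay blinded until final data entry, so it can be settled before results are seen. The cost is wider intervals and few degrees of freedom: with three groups per arm, PAC vs StEx has about 6 − 2 = 4.

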#### Participants

Recruitment (ongoing) will aim for 122 Portuguese breast cancer survivors who have completed primary cancer treatment and are currently under aromatase inhibitors therapy and will subsequently be randomized to receive the brief PA counseling (PAC), the structured exercise program (StEx), or to a waiting list control group.

The inclusion criteria for entering this study are: 1) post-menopausal women, below 70 years old; 2) histologically confirmed hormone-receptor-positive breast cancer (stage I, II, III); 3) having initiated AI hormonal therapy following the primary treatment (surgery, radiotherapy, chemotherapy, etc.), at least 1 month before being enrolled; and 4) ECOG-Performance Status 0–1 (being able to perform light-to-moderate physical activities). The exclusion criteria are: 1) evidence of stage IV cancer or synchronous tumors; 2) uncontrolled hypertension, cardiac or pulmonary disease; 3) contraindications to exercise training according to the assistant doctor; 4) inability to provide informed consent; and 5) expected inability to fulfill the proposed program schedule.

Given the study design, sample size estimations were calculated for primary outcomes having one-way factorial analysis of variance with repeated measures as the reference statistical analysis. Based on previous research findings, and considering a 25% dropout, the sample size was estimated in 98 participants to detect a small to moderate effect size (α = 0.05; statistical power = 0.80) using G*Power 3.1. Consensual criteria on sample size needs for mediator/moderator analyses are not consensual and depend on the procedure and number of indicators and pathways in the models; therefore, we increased the estimated number of participants in 25%, obtaining a final estimated sample size of 122 participants.

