#### Assessments

Participants will be assessed at four time points: baseline (T_0_), 4 months (intervention’s end; T_1_), and 10 and 16 months (T_2-_T_3_; during follow-up). A schematic description of all the measurements by timepoint is presented in Table 2. Assessments will take place in standardized conditions, at the exercise setting, in a calm comfortable environment, in small groups, with a group of study technicians attending every assessment period. At each assessment point, the research staff provides participants with an accelerometer, which they are required to wear for a week, and schedules an evaluation visit to the exercise setting, where participants complete the full battery of assessments, described below, and according to the assessment plan for that timepoint. An individual report with the assessment results will be provided to each participant at the end of each assessment period is complete. Participants will be contacted close to each assessment point to determine any changes in their contact or personal information that may have occurred, especially in the fulfillment of the eligibility criteria.

**Table 2 Tab2:** Measurements’ timeline

	**Intervention**		**Follow-up**	
	**T0 Baseline**	**T1 4 months**	**T2 10 months**	**T3 16 months**

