**Potential covariates**				
Treatment-related factors and demographics	X	-	-	-
AI Therapy length/continuation	X	X	X	X
Food intake	X	X	-	X

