##### Potential covariates

Demographics such as age, education level, professional status, marital status, smoking history, alcohol consumption, medical factors (i.e., breast cancer stage, cancer treatment types, time since diagnosis, time since treatment, length of AI therapy, comorbid conditions, and current medications, blood pressure, and resting heart rate) will be considered as potential covariates. Participant’s medical history will be confirmed by personal medical reports brought by participants. Given that dietary habits and caloric intake, unrelated to our interventions, may affect body composition, participants will complete the adapted version of the Dietary Instrument for Nutrition Education (DINE) [92]. DINE measures self-reported dietary behavior by examining the frequency of intake of 19 food/drink items (e.g., cheese, burgers/sausages, beef, pork/lamb, chips, bacon/ham, savory pies/snacks, fruits, vegetables, sweets, biscuits, sugary drinks, milk). Alcohol consumption and frequency of breakfast will also be assessed.

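### On its plain reading the repeated-measures ANOVA uses baseline as a time level, not a covariate, which costs precision on the 16-month arm contrasts

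*Protocol article*

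**What the plan says.** Statistical methods fixes the model as "Factorial Anovas with repeated measures". The full statement is: "Factorial Anovas with repeated measures, adjusting for potential covariates (e.g., primary treatment, length of AI therapy), will be conducted for primary and secondary outcomes". The Participants section bases the sample size on the same family, "having one-way factorial analysis of variance with repeated measures as the reference statistical analysis". The Assessments section sets the visits: "Participants will be assessed at four time points: baseline (T_0_), 4 months", then 10 and 16 months.

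Covariates appear in three places:
- Statistical methods gives the two examples in the sentence quoted above.
- The Potential covariates section lists demographic and medical factors, ending with "length of AI therapy, comorbid conditions, and current medications, blood pressure, and resting heart rate) will be considered as potential covariates", and adds diet.
- The covariate block of Table 2 has three rows: "Treatment-related factors and demographics", AI therapy length or continuation, and food intake.

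None of the three includes the baseline value of a primary outcome. Under Objectives, aim a concerns "long-term (16-month) effectiveness and cost-effectiveness of two 4-month group-based interventions" against the waiting list, and aim b compares the two interventions on long-term change. Table 2 shows a T0 measurement for every primary outcome except healthcare use.

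**The concern.** Baseline has to enter the stated model somewhere if the model is to test change. Since it is on no covariate list, the natural place is the time factor. With three arms and four levels of time, the treatment effect is then a group-by-time interaction with (3−1)×(4−1) = 6 degrees of freedom, and the 16-month comparison of two arms is a difference in T3−T0 change.

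According to Randomization and blinding, allocation follows the baseline assessments, so the arms have the same expected value at T0. A change score gives the baseline value a fixed weight of 1. A covariate model estimates the weight, and its variance is lower whenever the correlation is below 1. With 122 women planned over three arms, that difference can matter.

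The interaction test also combines 4, 10 and 16 months, so by itself it does not answer aims a and b, which are about the long term.

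**Working it through.** **Inputs from the article.** Three arms; four visits; alpha 0.05; target power 0.80; 25% dropout; 98 participants, raised to 122 (Participants, Assessments).

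**Inputs that are assumed.** The article describes the effect only as small to moderate and gives no SD, no correlation and no numeric allocation ratio. I assume equal allocation, a true difference of 0.5 SD at 16 months, equal variance σ² at T0 and T3, and rho from 0.3 to 0.8.

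**The plan's own figures.** 98 × 1.25 = 122.5, which agrees with 122. The 98 cannot be derived uniquely. One set of inputs reaches it: within-between interaction, 3 groups, 4 measurements, f = 0.15, rho = 0.5. The noncentrality is f²·N·m/(1−rho) = 0.0225 × 78 × 4/0.5 = 14.04, so N = 78 is the smallest multiple of 3 with power 0.80, and 78 × 1.25 = 97.5, or 98. Other sets come close too, so this is only weak support for the four-level reading.

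**Variance of the 16-month outcome term, per participant.**
- T0 as a time level (difference in change): 2σ²(1−rho)
- T0 as a covariate: σ²(1−rho²)
- Ratio, adjusted to change: (1−rho²)/[2(1−rho)] = (1+rho)/2

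**Group sizes.** All randomised: 122/3 = 40.7 per arm. With 25% lost: 40.7 × 0.75 = 30.5, taken as 30.

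**Power.** Noncentral t, two-sided 5%, 2n−2 degrees of freedom, noncentrality 0.5/√(2v/n), where v is the variance term with σ = 1. Example at rho 0.5 and n = 30: change 0.5/√(2×1.00/30) = 1.94, power 0.48; adjusted 0.5/√(2×0.75/30) = 2.24, power 0.59.

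| rho | v, change | v, adjusted | variance cut | power, 30 per arm | power, 40.7 per arm |
|---|---|---|---|---|---|
| 0.3 | 1.40 | 0.91 | 35% | 0.36 → 0.51 | 0.47 → 0.65 |
| 0.5 | 1.00 | 0.75 | 25% | 0.48 → 0.59 | 0.61 → 0.73 |
| 0.7 | 0.60 | 0.51 | 15% | 0.69 → 0.76 | 0.82 → 0.88 |
| 0.8 | 0.40 | 0.36 | 10% | 0.85 → 0.89 | 0.94 → 0.96 |

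At rho 0.5 and 30 per arm, the difference detectable with 80% power falls from 0.74 to 0.64 SD. Simulated three-arm, four-visit data with 40 per arm agree: 0.48, 0.58 and 0.82 for the T3−T0 contrast against 0.66, 0.72 and 0.86 with adjustment, at rho 0.3, 0.5 and 0.7.

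**If baseline were left out of the model altogether.** The variance is σ², so relative to adjustment it is 1/(1−rho²) = 1.10, 1.33 and 1.96 at rho 0.3, 0.5 and 0.7. Precision is lost on that reading too.

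**The omnibus test.** Take a 0.5 SD effect in both interventions, equal correlation between all visits, and no effect at T0. The sum of squares of the centred time profile is 4 × 0.25 × (1/4)(3/4) = 0.1875 for an effect at 4, 10 and 16 months (0, 0.5, 0.5, 0.5). It is also 0.1875 for an effect at 4 months that then vanishes (0, 0.5, 0, 0). The 6-df interaction therefore has the same power for both, and a significant result does not show that an effect was sustained.

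**The case against.** **The four-level reading is inferred.** A reader might take it as stated that T0 is a time level. It is not: no sentence names the levels of the time factor, and the covariate examples are an open list. A condensed article may also leave such detail to an analysis plan that is not shown. This stands as a caution. But the article does name the model, ties the sample size to it and lists covariates three times without the baseline outcome. The alternative of ignoring baseline also loses precision.

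**Baseline as a time level is not mere noise.** A reader might infer that T0 contributes nothing. That is wrong: a change score removes stable differences between women, and its variance 2(1−rho) is below the follow-up-only value of 1 once rho exceeds 0.5. At rho 0.7 and 30 per arm, power is 0.69 for change against 0.48 for follow-up alone. The defensible claim is only that adjustment does better than either.

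**Thirty per arm is not clearly the analysis set.** The plan is intention-to-treat with last observation carried forward, which could keep up to about 40 per arm. That is why both sizes are shown. The larger one treats filled-in values as if they had been observed.

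**The gains are not gains over the omnibus test.** Correct. With a constant effect and rho 0.7, the interaction test at 40 per arm has power of about 0.88, against 0.86 for simulated single-visit adjustment. At rho 0.3 and 0.5 it is lower (about 0.47 and 0.63, against 0.66 and 0.72). In no case is it a 16-month comparison.

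**Nothing is biased or contradictory.** Also correct. Repeated-measures ANOVA is valid under randomisation and fits aims worded as change.

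**Conclusion.** The point holds as one of efficiency and focus. On the plain reading, the planned contrast is a difference in change from baseline, and adjusting for T0 would reduce its variance by 10% to 35% over rho 0.8 to 0.3. The variance ratio needs no effect size, only equal variances at the two visits. The power figures also rest on the assumed 0.5 SD difference and equal allocation, and Randomization and blinding allows the allocation ratio to change.

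The gain in pairwise 16-month power is 12 to 18 percentage points at rho 0.3 to 0.5 and 2 to 7 points at rho 0.7 to 0.8. The article does not show where in this range the outcomes lie. It does not support calling the analysis biased or invalid. Separately, the omnibus interaction does not by itself answer aims a and b.

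**What to change.** State in Statistical methods that, for each outcome measured at T0, the main analysis is a longitudinal model of T1, T2 and T3 with arm, visit, arm-by-visit and the T0 value of the same outcome as covariate. An equivalent choice is a constrained longitudinal model with a common baseline mean across arms. Name the 16-month contrasts (each intervention against control, and PAC against StEx) with 95% confidence intervals as the main results. Any omnibus interaction test then becomes supportive. Exempt healthcare use, which has no T0 value.

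The cost is analysis wording only, since the T0 data are already in the assessment schedule. If an analysis plan already specifies baseline adjustment and the 16-month contrasts, a sentence in the article to that effect is enough.
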